# Low dose of morphine to relieve dyspnea in acute respiratory failure (OpiDys): protocol for a double-blind randomized controlled study

**DOI:** 10.1186/s13063-022-06754-3

**Published:** 2022-09-30

**Keywords:** Dyspnea, Opioids, Intensive care, Mechanical ventilation, Randomized controlled trial

## Abstract

**Background:**

Dyspnea is common and severe in intensive care unit (ICU) patients managed for acute respiratory failure. Dyspnea appears to be associated with impaired prognosis and neuropsychological sequels. Pain and dyspnea share many similarities and previous studies have shown the benefit of morphine on dyspnea in patients with end-stage onco-hematological disease and severe heart or respiratory disease. In these populations, morphine administration was safe. Here, we hypothesize that low-dose opioids may help to reduce dyspnea in patients admitted to the ICU for acute respiratory failure. The primary objective of the trial is to determine whether the administration of low-dose titrated opioids, compared to placebo, in patients admitted to the ICU for acute respiratory failure with severe dyspnea decreases the mean 24-h intensity of dyspnea score.

**Methods:**

In this single-center double-blind randomized controlled trial with 2 parallel arms, we plan to include 22 patients (aged 18–75 years) on spontaneous ventilation with either non-invasive ventilation, high flow oxygen therapy or standard oxygen therapy admitted to the ICU for acute respiratory failure with severe dyspnea. They will be assigned after randomization with a 1:1 allocation ratio to receive in experimental arm administration of low-dose titrated morphine hydrochloride for 24 h consisting in an intravenous titration relayed subcutaneously according to a predefined protocol, or a placebo (0.9% NaCl) administered according to the same protocol in the control arm. The primary endpoint is the mean 24-h dyspnea score assessed by a visual analog scale of dyspnea.

**Discussion:**

To our knowledge, this study is the first to evaluate the benefit of opioids on dyspnea in ICU patients admitted for acute respiratory failure.

**Trial registration:**

ClinicalTrials.govNCT04358133. Registered on 24 April 2020.

## Introduction

### Background and rationale {6}

Dyspnea is frequent and intense in intensive care unit (ICU) patients. Dyspnea is present in about half of the patients, whether they are intubated or not [1–5]. In intubated patients, median dyspnea is 50 mm on a visual analog scale ranging from 0 (no dyspnea), to 100 (maximum tolerable dyspnea) [1, 2]. Among non-intubated patients admitted for acute respiratory failure, 55% report moderate to severe dyspnea, and mean dyspnea is 40 mm on a visual analog scale [2, 3, 6].

Such dyspnea has an impact on the comfort, the prognosis, and the quality of life after ICU stay. In ICU patients, dyspnea is strongly and independently associated with anxiety [1–3, 7]. In intubated patients, dyspnea is associated with a longer duration of mechanical ventilation [1]. In patients who receive non-invasive ventilation, the persistence of moderate to severe dyspnea after the first non-invasive ventilation session is associated with higher mortality and longer length of stay [3]. Finally, dyspnea is one of the events participating in the genesis of post-traumatic stress disorder [2].

All these elements plead in favor of a better control of dyspnea in ICU patients. Opioids could find a major place here, as dyspnea and pain are central phenomena [8] with multiple analogies. Both are subjective phenomena and multidimensional sensory experiences with a visceral sensory component and an integrative emotional component. The right insular region appears to be specifically involved in the modulation of dyspneic sensory perception. This same region is activated by nociceptive stimuli [9]. The neurophysiological analogy between dyspnea and pain is thus clearly established by the existence of common afferences [10].

Opioids, whose analgesic properties are well known, also relieve dyspnea [11]. Reciprocally, pain stimulates ventilation, and its control could have beneficial effects on dyspnea [12]. These multiple analogies between dyspnea and pain have motivated the evaluation of the impact of opiates on dyspnea.

In the intensive care unit, the control of dyspnea implies in a first step to correct metabolic abnormalities and in a second step an optimal treatment of the condition causing the acute respiratory failure [7, 13]. In a certain number of patients, dyspnea persists despite all these attempts to relieve it. Opiates could find their place here, modulating the perception of dyspnea by decreasing the intensity of the central ventilatory command and the associated corollary discharge, thus modifying the central perception and possibly decreasing the anxiety [14]. The fear of overdose with respiratory depression has historically been the main obstacle to the widespread use of morphine for the relief of dyspnea in daily clinical practice. However, recent guidelines from the American College of Chest Physicians, the Canadian Thoracic Society [15] and the American Thoracic Society [16] advocate oral or parenteral administration of opioids for refractory dyspnea, which persist despite optimal treatment of the underlying affection.

Several meta-analyses have shown the benefit of morphine on dyspnea, but also its safety, as morphine administration has no impact on blood pressure, PaCO_2,_ or SpO_2_ in patients with end-stage onco-hematological disease, moderate to severe chronic obstructive pulmonary disease, or advanced heart failure [11, 17, 18], and this safety has been confirmed by several expert groups [16]. Randomized and non-randomized studies conducted in patients with terminal cancer, chronic obstructive pulmonary disease, heart failure, or idiopathic fibrosis have shown that morphine was associated with a significant decrease in dyspnea without inducing respiratory depression as suggested by unchanged respiratory rate, tidal volume, blood gas, and end-tidal PaCO_2_ [19–26].

### Objectives {7}

The primary objective of the trial is to determine whether the administration of low-dose titrated opioids, compared to placebo, in patients admitted to the ICU for acute respiratory failure with severe dyspnea decreases the mean 24-h intensity of dyspnea score. The secondary objectives include the evaluation of the impact of the administration of low doses of morphine on the incidence and severity of anxiety and pain every, and the evaluation of signs of intolerance to opioids.

### Trial design {8}

OpiDys is a phase 2 single-center parallel-group double-blind randomized placebo-controlled trial.

## Methods: participants, interventions, and outcomes

### Study setting {9}

The study will be conducted in a 22 beds medical ICU within the La Pitié-Salpétrière university hospital. See Fig. 1 for the trial study design and Table 1 for the steps of the trial.

**Fig. 1 Fig1:**
[figure not shown]
Trial study design

**Table 1 Tab1:** Description of the different steps from the inclusion visit to the end of the study

***Study steps***	***Day 0 (inclusion visit)***	***Day 0 to day 1 (every 4 h)***	***Day 1 (24 h)***	***End of study*** ***Day 2 (48 h)***
***Patient’s information***	***X***			
***Collection of consent***	***X***			
***Medical history***	***X***			
***Randomization***	***X***			
***Clinical examinations and scores***	***X***	***X***	***X***	***X***
***Respiratory support***	***X***	***X***	***X***	***X***
***Tolerance of respiratory support***		***X***	***X***	
***Intravenous titration of morphine/placebo***	***X***			
***Subcutaneous morphine/placebo relay***		***X***		
***Observance***	***X***	***X***	***X***	***X***
***Adverse events***		***X***	***X***	***X***
***Necessity of intubation***		***X***	***X***	***X***
***Nurse’s adhesion/satisfaction about the study***			***X***	

### Eligibility criteria {10}

Inclusion criteria are the followings:Adult patients ≤ 75 years,Admitted in intensive care for an acute respiratory failure defined as a respiratory rate> 24/min or signs of respiratory distress such as labored breathing or paradoxical inspiration, or SpO2 <90% in ambient air,Spontaneous ventilation, either under standard oxygen, high flow oxygen, or non-invasive ventilation,Dyspnea ≥40 mm on a Dyspnea-VAS from zero (no dyspnea) to 100 mm (worst possible dyspnea),Richmond agitation and sedation scale (RASS) between 0 and 2,No confusion, as defined by the Confusion Assessment Method for ICU (CAM-ICU), andSigned informed consent of the patient, a relative, or emergency consent process.

Non-inclusion criteria are the followings:Intubated patient or intubation planned upon admission,Unable to respond to a visual analog scale (hearing or visual impairment, insufficient command of French, previous psychiatric or cognitive disorders known),Moribund patient,Contraindication to opioids (known hypersensitivity to opioids, severe renal insufficiency (creatinine clearance <30 ml/min), severe hepatocellular insufficiency (factor V <50%)Any formal contra-indication of opiates,Opioid use within the 24 h before inclusion,Pregnancy or breastfeeding,Minor and protected adult,Exclusion period due to inclusion in another clinical trial,Previous inclusion in this study, andNo affiliation to social security.

### Who will take informed consent {26a}

Prospective patients will be orally informed by the principal investigator and provided with a written information sheet. Signed informed consent will be obtained by the investigator who remains independent from the physician in charge of the patient.

### Additional consent provisions for collection and use of participant data and biological specimens {26b}

Not applicable; no samples were collected.

## Interventions

### Explanation for the choice of comparators {6b}

Morphine hydrochloride is an opioid that is commonly used in hospitals to control pain. It can be administered either intravenously or subcutaneously. The placebo arm will act as a control group for the opioid arm.

### Interventions description {11a}

The experimental group will receive an intravenous titration of morphine at an initial dose of 2 mg, followed by 1 mg every 3 min until Dyspnea-VAS is <40 mm, with a maximum safety dose of 8 mg. Once the target (Dyspnea-VAS <40 mm) or the maximum safety dose is reached, morphine hydrochloride will be relayed subcutaneously (due to the longer half-life of this way of administration). It will initially be administered at a dose of 5 mg immediately at the end of the intravenous titration and then every 4 h for a total of 24 h, according to the dyspnea recorded on the visual analog scales. Dose of subcutaneous morphine will be increased from the previous one by increments of 2.5 mg when the dyspnea evaluated by the visual analog scale is greater than or equal to 40, without exceeding the maximum dose of 10 mg every 4h. It will be reduced in steps of 2.5 mg every 4 h if the dyspnea VAS remains below 40 mm. The total duration of subcutaneous treatment will be 20 h.

The control group will receive a placebo NaCl 0.9% administered according to the same protocol as the experimental arm.

All other treatments will be similar in both groups and will follow national or international guidelines.

### Criteria for discontinuing or modifying allocated interventions {11b}

Morphine hydrochloride will be discontinued in case of nausea ≥ grade 3, constipation ≥ 4, bradypnea < 12/minute, delirium, drowsiness, or alteration of the level of consciousness defined by a Glasgow Coma Scale ≤ 9.

### Strategies to improve adherence to interventions {11c}

**For patients being hospitalized in the ICU, adherence to intervention should be correct.**

### Relevant concomitant care permitted or prohibited during the trial {11d}

All standard practices will be continued throughout the study period. The only intervention prohibited is the administration of opioids other than those given for the need of the protocol.

### Ancillary and post-trial care {30}

Ancillary and post-trial care is not planned.

### Outcomes {12}

#### Primary outcome measure

Average dyspnea over 24 h (Time frame: systematically evaluated every 4 h over 24 h and whenever necessary). Dyspnea will be assessed by VAS-dyspnea (ranging from zero, no dyspnea to 100, worst possible dyspnea), which is a patient-reported outcome (PRO).

#### Secondary outcome measures

Intensity of dyspnea, every 4 h over 24 h, on a Dyspnea-VAS from 0 to 100 mm (worse) (PRO)Incidence of severe dyspnea after the target dyspnea is reached (Dyspnea-VAS ≥40 mm) over 24 h (PRO)Intensity of anxiety every 4 h over 24 h, on an Anxiety-VAS from 0 to 100 mm (worse) (PRO)Incidence of moderate to severe anxiety (Anxiety-VAS ≥40 mm) over 24 h (PRO)Intubation rate within the first 48 hIncidence of impaired alertness defined by Glasgow Coma Scale ≤ 12, over 48 hIncidence of coma over 48 hIncidence of delirium over the first 48 hRespiratory rate every 4 h over the first 24 hProportion of patients requiring the transition from one oxygenation technique to another within 24 hIntensity of pain every 4 h over 24 h, on a Pain-VAS from 0 to 100 mm (worse)Duration of night sleep the first night (PRO)Quality of sleep during the first night (PRO) evaluated at the end of the first night with by a VAS from 0 (min) to 100 mm (worse)Severity of dry eye (PRO) in the first 24 h evaluated by a VAS from 0 (min) to 100 mm (worse)Severity of dry nose (PRO) in the first 24 h evaluated by a VAS from 0 (min) to 100 mm (worse)Severity of feeling of gastric distension (PRO) in the first 24 h evaluated by a VAS from 0 (min) to 100 mm (worse)Constipation (PRO) in the first 48 h evaluated by a VAS from 0 (min) to 100 mm (worse)Nausea (PRO) in the first 48 h evaluated by a VAS from 0 (min) to 100 mm (worse)Nurses' adherence to the protocol in the first 24 h evaluated by a VAS from 0 (min) to 100 mm (worse)Nurses' satisfaction with the protocol in the first 24 h evaluated by a VAS from 0 (min) to 100 mm (worse)Number of non-invasive ventilation sessions in the first 24 hTotal duration of non-invasive ventilation in the first 24 hTolerance of non-invasive ventilation (PRO) in the first 24 h evaluated by a VAS from 0 (min) to 100 mm (worse)Duration of HFNCO (high-flow nasal cannula oxygenation) in the first 24 hTolerance of HFNCO (high-flow nasal cannula oxygenation) in the first 24 hDuration of standard oxygen in the first 24 hTolerance of standard oxygen (PRO) in the first 24 h evaluated by a VAS from 0 (min) to 100 mm (worse)Any adverse or serious event occurring within the first 48 h, number of adverse events

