## Statistical methods

### Statistical methods for primary and secondary outcome {20a}

#### Primary outcome

The comparison between the two treatment groups of the mean dyspnea during the first 24 h will be performed by a Mann Whitney test taking a one-sided alpha risk of 10% to limit the risk of missing a difference. The primary outcome will be analyzed in the modified intent to treat population considering all patients randomized having received at least one dose of intervention in the group in which they will be randomized.

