#### Secondary outcomes

Quantitative variables will be compared between the two arms with a Mann-Whitney test. Categorical variables will be compared between the two arms with a chi-square test or a Fisher’s exact test as appropriate.

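### The secondary outcome of severe dyspnea after the target is reached depends on a post-randomisation response, so never-relieved patients in either arm cannot have the event and the between-arm comparison is distorted

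*Protocol article*

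**What the plan says.** The outcome is one line in the protocol article, under Secondary outcome measures: "Incidence of severe dyspnea after the target dyspnea is reached (Dyspnea-VAS ≥40 mm) over 24 h (PRO". Other sections determine how it behaves.

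- Eligibility criteria {10} require "Dyspnea ≥40 mm on a Dyspnea-VAS from zero (no dyspnea) to 100 mm (worst possible dyspnea", so no patient is at target when randomised.
- Interventions description {11a} gives an initial dose "followed by 1 mg every 3 min until Dyspnea-VAS is <40 mm". The next stage begins "Once the target (Dyspnea-VAS <40 mm) or the maximum safety dose is reached", so titration can end without the target being met.
- The same section applies this rule to placebo: "The control group will receive a placebo NaCl 0.9% administered according to the same protocol as the experimental arm".
- Secondary outcomes, under Statistical methods {20a}, states: "Categorical variables will be compared between the two arms with a chi-square test or a Fisher’s exact test as appropriate".
- The analysis set, defined for the primary outcome and applied to the trial as a whole in {20c}, is the "modified intent to treat population considering all patients randomized having received at least one dose of intervention" (mITT below).

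No incidence of severe dyspnea without the condition is listed. The anxiety outcome in the same list is an incidence at 40 mm or more over 24 h with no such condition.

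**The concern.** The event requires two steps: falling below 40 mm, then returning to 40 mm or more. The first step happens after randomisation and is what the study drug is meant to bring about. A patient who stays at or above 40 mm for all 24 h has the worst possible course but cannot have the event.

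There are two ways to treat such patients, and neither restores a fair comparison. If they stay in the denominator, they count as successes. If they are left out, the arms are compared among patients selected by their response, and randomisation no longer protects the comparison.

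Time at risk also differs. Titration from 2 mg to 8 mg in 1 mg steps takes six steps of 3 minutes, or 18 minutes. A patient relieved by then is exposed to the event at all six later 4-hourly readings; one first relieved at 12 h is exposed at only three (16, 20 and 24 h).

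At stake is the reading of the only listed incidence of severe dyspnea, in a pilot meant to provide a signal of effectiveness for a larger trial.

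**Working it through.** **Figures in the plan.** None is given for this outcome. The only figure to reproduce is the sample size: 2 × [26 × (1.2816 + 0.8416) / 25]² = 9.75 per arm; divided by the Mann-Whitney efficiency of 0.955 this is 10.2, so 11 per arm and 22 in total, as stated. Each arm therefore has 11 patients.

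**Algebra.** Let r be the proportion reaching the target and q the proportion of those who return to 40 mm or more (relapse).

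- Outcome as worded, over all patients: E = r × q.
- Relapsed or never relieved: U = r × q + (1 − r).
- Hence U − E = 1 − r. The wording removes the never-relieved share from each arm, and the placebo-minus-morphine difference falls by exactly r(morphine) − r(placebo). It is undistorted only if reach is equal.

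**Range.** The reach and relapse rates are assumptions, since the protocol gives none. All results are morphine v placebo.

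| Reach | Relapse | As worded (E) | Relapsed or never relieved (U) |
|---|---|---|---|
| 90% v 40% | 50% v 50% | 45% v 20% | 55% v 80% |
| 80% v 30% | 50% v 50% | 40% v 15% | 60% v 85% |
| 90% v 30% | 40% v 70% | 36% v 21% | 46% v 91% |
| 90% v 50% | 40% v 60% | 36% v 30% | 46% v 80% |
| 90% v 70% | 40% v 60% | 36% v 42% | 46% v 72% |
| 80% v 80% | 40% v 60% | 32% v 48% | 52% v 68% |

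First row: 0.90 × 0.50 = 0.45 and 0.40 × 0.50 = 0.20; adding the never-relieved 0.10 and 0.60 gives 0.55 and 0.80. The first four rows reverse direction. The fifth keeps its direction but shrinks from 26 to 6 points. The last, with equal reach, keeps its 16 points.

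**Link to the planning figures.** Sample size {14} assumes 24-h means of 12 and 37 mm with SD 26. As a rough proxy for reach, P(24-h mean < 40) is Φ(28/26) = 86% for morphine and Φ(3/26) = 55% for placebo. With an assumed 40% relapse in both arms, E is 34% v 22% and U is 48% v 67%. Placebo relapse would have to exceed 0.86 × 0.40 / 0.55, about 63%, before morphine looked better as worded.

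**Model with benefit throughout the 24 h.** Equal relapse ignores any benefit after titration. A second check simulated an end-of-titration reading and six 4-hourly readings around the planned means (SD 26), with an assumed within-patient SD of 5 to 20 mm and no time trend. It used normal data, without the 0 to 100 limits or the entry threshold. The two figures in each range belong to within-patient SD 5 and 20.

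| Outcome | Placebo | Morphine |
|---|---|---|
| As worded, target met at end of titration, all patients | 10–34% | 7–29% |
| As worded, target met at any reading, all patients | 19–62% | 11–42% |
| Any reading from 4 to 24 h at 40 mm or more | 55–79% | 21–46% |

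Morphine looks better in each row. The difference is 33 to 34 points for the unconditional outcome (55 − 21 and 79 − 46), but 3 to 5 points (10 − 7 and 34 − 29) or 8 to 20 points (19 − 11 and 62 − 42) as worded.

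**Reachers only.** With the 86% and 55% proxies, about 9 v 6 patients remain. A separate simulation with assumed severity, a 25 mm effect at titration and no later drug effect gave reach of 83% v 26% and relapse among reachers of 57% v 32%, so selection alone made morphine look worse. A later benefit of 10 mm changed this to 30% v 32%, and one of 25 mm to 6% v 32%.

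**The case against.** The strongest reply is that reversal depends on the inputs chosen. Low placebo reach with equal relapse is an extreme: the planned control mean of 37 mm is already below the target, and subcutaneous dosing continues after titration, so lower relapse on morphine is what the sponsor expects. Under the planning figures with no trend, morphine looks better. This stands. A reader might infer that the outcome will make morphine look worse, or that only placebo patients are affected. The documents support neither: they give no reach or relapse rates, and never-relieved morphine patients are treated identically. A steadily falling placebo course could still produce reversal, so it cannot be excluded.

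Second, the denominator may be set in a statistical analysis plan that is not shown. That also stands, and its absence is not criticised here. The condition itself is in the protocol's definition, and neither denominator removes it. If the sponsor meant after titration has ended, the text does not say so.

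Third, recurrence after relief is a legitimate description of how long relief lasts. It is, but as a description among patients who were relieved, not as a tested contrast between randomised arms.

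Fourth, this is one item in a long secondary list of a 22-patient pilot. The primary outcome and the 4-hourly intensity outcome carry no such condition and would show unrelieved patients directly. This limits the weight of the point.

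**Conclusion.** The point holds as a flaw in one secondary outcome. By definition, a patient in either arm who never falls below 40 mm cannot have the event, and the planned between-arm test is distorted when the arms differ in who reaches the target. If the drug had no effect at all, the outcome would be distributed alike in both arms; the problem arises when morphine works.

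The likely consequence is an understated benefit. In the model built on the planning figures, a difference of 33 to 34 points shrinks to 3 to 5 or 8 to 20 points, depending on when the target must be met. Reversal occurs for some assumed rates (45% v 20%) and not for others (36% v 42%), so it is a possibility only. All these sizes rest on assumed reach, relapse and within-patient variation. Nothing here touches the primary analysis or the sample size.

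**What to change.** Define the compared outcome as any scheduled Dyspnea-VAS reading from 4 to 24 h of 40 mm or more, in all mITT patients. Never-relieved patients then count as events, and dyspnea is put on the same footing as the anxiety outcome. This also counts patients relieved late whose early readings were still at 40 mm or more, which is appropriate for an incidence over 24 h. Report the proportion reaching the target by arm, and keep relapse among those who reached it as descriptive, without a between-arm test.

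No new data are needed, because the scale is already recorded every 4 h for 24 h. The cost is an amendment to the outcome wording. Recruitment has begun (first patient in December 2020), and section {25} requires outcome changes to be communicated to investigators, the ethics committee, participants and registries. The new outcome overlaps somewhat with the 4-hourly intensity outcome. How readings after intubation or death are scored is a separate choice that this change does not settle.
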